## **1. Background and rationale**

Chronic obstructive pulmonary disease (COPD) is a pervasive disease that is estimated to affect 2.6 million Canadians (17%) aged 35 to 79 have COPD (Government of Canada, 2014) costing the health care system in Canada 1.5 billion annually (Mittmann et al., 2008). Ontarians living with COPD are frequent users of the health care system and account for 24% of hospital admissions and 24% of emergency department (ED) visits (Gershon, Guan, Victor, Goldstein, & To, 2013) and COPD is responsible for the highest percentage (18.8%) of 30-day readmissions to ED in the province (Government of Canada, 2017).

It has been demonstrated that sources of care beyond the hospital (e.g. home care or outpatient clinics) that are aligned with a comprehensive discharge plan are effective ways of reducing hospital readmissions for COPD (Ko et al., 2014). As a result, care for COPD patients has been moved to the community and local health care clinics, such as Markham Stouffville Hospital (MSH), who are tasked with follow up care for COPD patients. However, access to these services remains a challenge due to funding restrictions. For example as per our communication with the hospital, the outpatient clinic can see no more than 600 patients per year, which places pressure on patients to self-manage their condition with limited supports. Local community centres are often tasked with providing support to self-manage COPD at home, but limited resources makes it challenging and there is a need to optimize self-management.

*Self-management* is a person's ability to manage the clinical and psychosocial effects of their chronic condition and their ability to make lifestyle adaptations inherent in living with a chronic condition (McBain, Shipley, & Newman, 2015). A recent Cochrane review of self-management interventions in COPD (face-to-face, not technology based and not studies that involved physiological recordings) concluded that they are associated with improved quality of life and a reduction in hospital admissions (Zwerink et al., 2014). A foundational component of self-management is "self-monitoring", defined as "the patient undertaking one or more of the following activities (i) self-measurement of vital signs, symptoms, behaviour or psychological well-being; (ii) self-interpretation of this data; or (iii) self-adjustment of medication, treatment, lifestyle or help-seeking behaviour as a result of self-awareness and/or self-interpretation (McBain et al., 2015). COPD patients often have difficulty detecting early deterioration in their symptoms. Self-monitoring programs may provide the means of monitoring patients' in the community allowing for detection of deteriorations quicker and for an intervention before significant deterioration occurs (Rojahn et al., 2016).

*Technology-enabled* self-monitoring still requires patients to take self-measurements, but also has the potential to remove the self-interpretation and self-adjustment components of self-monitoring from the responsibility of the patient. This can be achieved by the technology (e.g. a tablet software program) registering the readings of the patients, interpreting the data and providing automatic feedback to patients about the type of adjustments they need to make. This feedback has the potential to allow patients to learn about their condition and to recognize their symptoms early on. Currently, most technology-enabled self-monitoring programs also transmit the data to a healthcare professional who monitors the data remotely (*remote-monitoring*) and contacts the patient when needed (Cruz, Brooks, & Marques, 2014).

The benefits of remote monitoring are quite well established. A recent Cochrane meta-analysis concluded that remote monitoring has shown promise in reducing acute care utilization and

reducing the number of exacerbations in COPD patients (McLean et al., 2012). Studies of remote monitoring have reported lower emergency admission rates (De San Miguel, Smith, & Lewin, 2013; Pedone, Chiurco, Scarlata, & Incalzi, 2013; Steventon et al., 2012), up to 50% reductions in inpatient admissions (Brown Connolly, 2014) and reductions in length of stay (Clarke, Fursse, Connolly, Sharma, & Jones, 2017; De San Miguel et al., 2013). Remote monitoring can also lead to improved patient's knowledge and self-efficacy. For example, Rixon et al. (2015) showed that patients reported better emotional functioning and mastery 1 year after the implementation of a remote monitoring program.

Some have argued, however, that the benefits of self-monitoring programs lie in the remote-monitoring component (the direct contact with a healthcare provider) (McBain et al., 2015). The authors acknowledge, however, that this has not systematically been studied, especially in the COPD patient population. Furthermore, this has not been studied in a *technology-enabled* self-monitoring program that provides feedback to patients.

Furthermore, technology-enabled self-monitoring programs with patient feedback have a great cost-saving potential. As such, remote monitoring is expected to reduce healthcare utilization and cost (Haesum et al., 2012). However, preliminary studies on the cost-effectiveness of these programs have provided mixed results. Some studies have suggested that it can lead to reduction in costs (De San Miguel et al., 2013), while others have reported that the cost-effectiveness of the programs is not clear (Clarke et al., 2017). One significant cost associated with remote monitoring programs is the labor cost associated with paying a clinical health provider to monitor patients' recordings. Self-monitoring does not involve remote monitoring and as such its cost per patient is lower than remote-monitoring. If technology enabled self-monitoring with patient feedback can be demonstrated to be as effective as remote monitoring, then the savings for administering such a program can be substantially reduced.

In summary, technology-enabled self-monitoring programs have the potential to educate patients about their condition, teach them how to self-manage and have the potential to significantly reduce costs.

## **2. Research Objectives**

Therefore, the goal of the current project is to investigate the effectiveness of implementing a technology-enabled self-monitoring program (SM group) or a technology enabled self- and remote-monitoring program (RM group) in a COPD patient population compared to standard of care. Effectiveness will be measures by outcomes examining patients' self-management skills, quality of life, COPD knowledge and respiratory symptoms. The standard of care group (SC group) currently does not use any technology to monitor patients at their home. Therefore the following 3 conditions will exist in the study:

1. SM group: Patients in this group will be recording their vitals and symptoms with the Cloud DX platform everyday and will be provided with an action-plan that instructs them on what to do in response to their readings.
2. RM group: Patients in this group will be recording their vitals and symptoms with the Cloud DX platform everyday and will be provided with an action-plan that instructs them on what to do in response to their readings. In addition, a respiratory therapist (RT) will be monitoring asynchronously their vitals and contacting them when their vitals exceed pre-determined thresholds. The RT will also check on patients once a week irrespective of the value of the vitals.

3. SC group: patients will not be provided with a technology or an action plan (as the action plan is based on vitals and symptoms).

### **3. Trial design**

We will use a mixed methods design for this study, containing both a quantitative and a qualitative component. The quantitative component is presented first and the qualitative component follows. An open-label randomized controlled trial will be used for this study. Patients will be randomized to one of 3 groups: a RM, a SM intervention group and a SC group (41 patients per group).

### **4. Methods**

#### **a. Study Setting**

The study will be conducted at Markham Stouffville Hospital (MSH) with most patients being recruited from the Outpatient COPD Clinic (Respiratory Health-COPD Clinic). Recruitment will be coordinated internally by the clinical project specialist, who is also a respiratory therapist. Some patients will also be identified through inpatient admission records and the Health for All Family Health Team (FHT) by their family doctors who have clients that are living in the community with diagnosed COPD. Additional patients will be recruited by respirologists. These respirologists practice at the Outpatient COPD clinic, but also have separate private practices in Markham. Finally, patients will be recruited from the Outpatient COPD Exercise Rehabilitation Program that is run at the Cornell Community Centre in collaboration with MSH. These patients will be approached by an MSH respiratory therapist who coordinates the rehabilitation program. We have already established a research collaboration with the hospital during the design phase of this project that informed our methods and recruitment practices. Access to potential patients will be determined locally, in-house at MSH by the clinical project specialist, who is also a respiratory therapist. All data collection will be done internally at MSH. All initial contact will be done internally to the site from where the patient is originating (e.g. Outpatient COPD Clinic, COPD rehabilitation program, Family Health Team (FHT), or a respirologists' private practice). For sites that are outside MSH, patients will be provided with the brochure for the study and will be asked for permission to be contacted by the clinical project specialist.

#### **b. Eligibility criteria**

To be included in the study patients need to be at least 18 years of age and have a clinical diagnosis of COPD that has been established by their respirologist as per clinical guidelines (Dewar & Whit R. Curry, 2006). Exclusion criteria include a diagnosis of other significant lung disease (e.g. interstitial lung disease) or dementia, patients without wifi at their home, patients who do not speak English (required for filling out the questionnaires) or patients unable to use the technology due to physical or cognitive impairment.

#### **c. Recruitment**

Recruitment will be on-going until 123 patients have been recruited for the intervention phase (see sample size justification in Section 6.b). Patients will be approached by the clinical staff (respirologist or respiratory therapist-RT) who will introduce the technology to them and provide them with brief information about the trial with a brochure (Appendix 19) and request permission to pass the patient's information to the clinical project specialist at MSH. At this time the consent

form will also be given to give the patients enough time to consider participation. The clinical project specialist will later call the participants to further inquire about their interest in participating and to provide further details about the project. At this time they will also confirm the patient has a copy of the consent form and if they don't have the clinical project specialist will email it to the patient. The patients who are still interested in the project will be scheduled for their baseline evaluation, at which time informed consent will be signed (Appendix 1) and the Cloud DX kit will be provided to them. Patients can split that session into two, if they feel it is too much for one visit. There will also be a recruitment video that will be uploaded on YouTube. The clinical project specialist will email the link with the brochure to interested patients. The clinical project specialist will also be showing the video on a tablet to patients in the Outpatient COPD Exercise Rehabilitation Program. The Inpatient RT will show the video on a tablet to patients with COPD prior to their discharge from hospitalization.

#### d. Intervention

Patients will be randomized to either SM, RM group or SC group (41 patients per group). Patients in the SM and RM group will receive the Cloud DX kit at the start of the trial and will continue using it for 6 months. Patients in the SC group will be given the opportunity to receive the kit at the end of the trial and use it for free for 6 months (see Figure 1). All patients will complete 3 assessments: at baseline, 3 months and 6 months on a series of questionnaires (see Outcome section for a list and description). They will also complete a demographic questionnaire at the initial visit (Appendix 13). The clinical project specialist at MSH will be responsible for collecting all data at each visit. The initial visit is expected to take 2 hours, allowing for obtaining consent, an introduction of the kit, and survey completion. Subsequent visits are expected to take about 1 hour to complete, as only surveys will be filled out. Visit 2 and 3 will be done in-person or remotely as surveys will be completed through REDCap and patients will have the option to complete them online from their home or over the phone. The clinical project specialist will make contact with the patient via telephone to remind them of the survey deadline. If patients prefer to come in person, they will be provided with that option. If the patient prefers to conduct the survey over the phone, they will be transferred over to the research team at WCH with a script (Appendix 20). Once the patient verbally agrees, the clinical project specialist at MSH will call one of the Research Assistants at WCH to provide the patient name, telephone number, and email address (if applicable). If the Research Assistant does not pick up, a voice message will be left on the Research Assistant's password protected mailbox. The Research Assistant then documents patient information in a password protected Excel document in the WCH internal drive. The Research Assistant will then contact the patient to conduct the survey as well as email the patient for any follow-up requests from the phone call, ie. to resend the REDCap survey link.

Patients in the SM and RM group will also be contacted by the clinical project specialist 2 weeks after receiving their kit to review whether their thresholds have been set properly. If a revision of the thresholds is needed this will be done with the respirologist's approval.

In addition, the clinical project specialist at Markham-Stouffville Hospital will conduct a chart review to collect patient characteristics listed in the Appendix 21 - Patient Characteristics Collected from Chart Review.

Figure 1. Patient flow through the study.

[figure not shown]

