### **The Cloud DX Kit**

The technology we will use in the study is the Cloud DX Connected Health Kit. All patients will be provided with the Cloud DX Connected Health Kit as a tool for self-monitoring and asynchronous remote monitoring. It consists of a custom Tablet computer, Pulsewave® wrist cuff monitor (Health Canada license, Appendix 2), Oximeter (Health Canada license, Appendix 3), Scale and Thermometer (Health Canada license, Appendix 4). Cloud DX is also a licensed distributor of medical devices (MDEL: 6984, Appendix 5). Patients are also provided with a comprehensive user manual (Appendix 6). All of these devices are optimized to work together, pre-paired and ready to go out of the box. All patients will use the kit to record daily their physiological and symptom readings. All patients will also answer general questions about their symptoms, by filling out a digital version of the COPD Assessment Test (CAT, Appendix 7) (Jones et al., 2009) and MRC scale (Stenton, 2008) (Appendix 8). The Pulsewave wrist cuff measures blood pressure, heart rate, breathing rate and detects cardiac anomalies with comfort and ease of use.

All patients in the RM and SM group will also be provided with an action plan document that will be given on a piece of paper. This document consists of a chart that instructs patients on what to do if their readings fall outside their respirologist pre-specified values. The action plan includes actions such as calling the clinic, filling out a prescription or going to the emergency department (see Appendix 17).

For patients assigned to the RM group, if a patient's readings fall outside the pre-determined thresholds, a notification will be sent to the clinical project specialist at MSH and to the patient through email notifying them that the reading exceeded the threshold. Patients in the RM group will also receive a follow-up call from the clinical project specialist whenever their readings exceed thresholds. The follow-up calls will be done only Monday to Friday 9-5. An attempt to complete the follow-up call will be done within 24 hours of receiving the notification and a message will be left to call back the clinical project specialist if patients are not available when that call is made. The purpose of the call is to check on the patients, to encourage them to follow their action plan and to use the call as an educational opportunity to teach patients about

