#### e. Outcomes

##### i. Primary Outcome

- *The Partners in Health (PIH) scale* (Petkov, Harvey, & Battersby, 2010) (Appendix 9). A validated scale measuring the current status of self-management, with items on knowledge of the condition and skills to monitor and respond to symptoms.

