#### g. Data Collection

All assessment data will be collected by the clinical project specialist at MSH and entered into a de-identified database that will be then sent to the research coordinator at Women's College Hospital. The clinical project specialist will also assign a Cloud DX ID that will be distinct from the REDCap ID. REDCap IDs will be consecutive, while Cloud DX IDs will be random, so that they cannot be easily linked to each other. All data will be entered into REDCap by the clinical project specialist.

Data collected through the chart review will be collected and tracked using the Health Care Utilization Chart Review Tool (Appendix 22 - COPD Cloud DX Health Care Utilization Chart Review Tool).

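### The unblinded specialist who coaches the RM arm is also named collector of the self-reported PIH, and no rule places baseline PIH before allocation or kit introduction

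*Protocol*

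**What the plan says.** **Blinding.** Section 3 of the Protocol: "An open-label randomized controlled trial will be used for this study".

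**Who collects.** Section 4.d: "The clinical project specialist at MSH will be responsible for collecting all data at each visit". Section 4.g: "All assessment data will be collected by the clinical project specialist at MSH and entered into a de-identified database". Section 4.g also has this specialist enter all data into REDCap.

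**Who coaches.** The Cloud DX Kit section: "Patients in the RM group will also receive a follow-up call from the clinical project specialist whenever their readings exceed thresholds". Among the purposes of the call are "to encourage them to follow their action plan and to use the call as an educational opportunity to teach patients about" COPD. The specialist also screens RM data weekly.

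**Primary outcome.** Section 4.e describes the PIH scale as "A validated scale measuring the current status of self-management, with items on knowledge of the condition and skills to monitor and respond to symptoms".

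**Follow-up routes.** For visits 2 and 3, section 4.d lets the patient choose between attending in person, completing the REDCap survey from home, and the phone. For the last of these: "If the patient prefers to conduct the survey over the phone, they will be transferred over to the research team at WCH". The specialist makes the reminder call.

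**First visit.** Section 4.d gives it two hours, "allowing for obtaining consent, an introduction of the kit, and survey completion". Section 4.c provides the kit at the baseline evaluation and lets patients split that session in two. Section 4.d gives standard-care (SC) patients the kit only at the end of the trial.

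**The concern.** Two separate weaknesses bear on the primary comparison.

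**Collector and coach are one person.** In the RM arm the specialist teaches patients about COPD and urges use of the action plan, and is then the named collector of a scale on knowledge and on monitoring and responding to symptoms. Patients may rate themselves more favourably to the person who taught them. SC patients have no such relationship. Because the patient picks the follow-up route, the mix of routes could also differ by arm.

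**Baseline timing is open.** Baseline PIH is one of the time points compared in the planned repeated-measures ANOVA. If it were completed after allocation was known, or after the kit was introduced in the self-monitoring (SM) and RM arms only, the starting score would already carry part of the intervention.

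Neither distortion can be separated from a treatment effect once the data are in.

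**Working it through.** **1. Who collects the follow-up questionnaires?**

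| Source | Collector at 3 and 6 months |
|---|---|
| 4.d, general statement | Specialist, everything |
| 4.g | Specialist, all assessment data and all REDCap entry |
| 4.d, online route | Patient, directly in REDCap |
| 4.d, phone route | WCH research assistant |
| 4.d, in-person route | Not restricted, so the specialist |

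The first two rows do not fit the third and fourth. The last row is where the coach remains the collector. The phone handover lists name, telephone number and email address. Arm is not on that list, but no sentence says that the assistants are kept unaware of it.

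**2. When is baseline PIH taken?** Section 4.d names consent, kit introduction and survey as the contents of one visit. Section 4.c puts kit provision at the same evaluation and allows two sessions. No sentence places the survey before randomisation or before the kit. Figure 1, the patient flow, is not available in the text reviewed, so it cannot settle the order.

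**3. How sensitive is the comparison to a small shift?**

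Inputs from the Sample Size section (4.f): 41 per arm, correlation 0.85, alpha 0.05 (sidedness not stated), effect 0.42 SD for PIH. The shift is an assumption; the documents give none.

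The plan's own power comes first. It states 0.97 (PIH) and 0.71 (SGRQ). A one-sided change-score t-test gives 0.964 and 0.715, so the inputs are understood. A two-sided test gives 0.929 and 0.597. The figures below are two-sided.

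Standard errors of the RM–SC difference, in SD units:
- baseline-adjusted: √(1 − 0.85²) × √(2/41) = 0.527 × 0.221 = 0.116
- change score: √(2 × (1 − 0.85)) × √(2/41) = 0.548 × 0.221 = 0.121

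With no true effect, the rejection rate is P(|Z + shift/SE| > 1.96) for the baseline-adjusted form and its noncentral-t equivalent (80 df) for the change score.

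| Shift in exposed RM patients (SD, assumed) | Baseline-adjusted, all exposed | Change score, all exposed | Baseline-adjusted, half exposed |
|---|---|---|---|
| 0.10 | 13.8% | 12.9% | 7.1% |
| 0.15 | 25.2% | 23.2% | 9.9% |
| 0.20 | 40.5% | 37.2% | 13.8% |

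The last column halves the mean shift (0.05, 0.075, 0.10), assuming that only half of RM patients give their answers to the specialist.

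For the baseline question, suppose kit exposure raised baseline PIH in the kit arms by 0.10, 0.15 or 0.20 SD. A true effect of 0.42 would then show as 0.32, 0.27 or 0.22, and two-sided change-score power would fall from 92.9% to 74.3%, 59.7% or 43.5%. If exposure lowered the self-rating instead, the effect would be overstated.

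**The case against.** The strongest reply is that the plan already deals with much of this. Coaching can affect only the 3- and 6-month scores, and for those the patient may answer online or to a WCH assistant. Nor is collecting shown to mean interviewing: the Protocol speaks of patients completing and filling out the questionnaires. SC patients also meet the specialist, through the recruitment call, the baseline visit and the reminders.

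This stands in part. A reader might infer that RM patients generally report their skills face to face to their coach; the documents do not say so. They do leave that route open, at the patient's choice, and two general statements assign all collection to the coach.

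On baseline, a reader might infer that PIH is planned after kit training. The wording lists what two hours must cover; it does not fix a sequence. Clinical staff also introduce the technology to every approached patient before consent, and the kit sentences in section 4.c and at the start of the Cloud DX Kit section carry no arm restriction, so even a difference in exposure between arms is not certain. What stands is that no rule excludes it.

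On size, the shift is wholly assumed. Part of any reporting shift would come from patients' own knowledge of their arm, which no change of collector removes. The baseline-adjusted figures also come from a model other than the planned repeated-measures ANOVA. These points are right, and the figures are therefore illustrative only.

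**Conclusion.** The point holds in limited form. The text establishes three things: the RM coach is the named collector of a self-reported primary outcome in an open-label trial; that assignment does not fit the online and WCH phone routes in the same section; and in-person follow-up remains with the coach, with a mode that may differ by arm. The absence of a rule on baseline timing is also established. That baseline scores will be contaminated is not, and neither is the direction of any such bias.

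A reader might also infer that the RM effect will be inflated, or that the true type I error is near 40%. The documents support neither. The rates of about 13–14%, 23–25% and 37–41% are upper values under an assumed shift of 0.10, 0.15 or 0.20 SD affecting every RM patient. With half exposed they are about 7%, 10% and 14%. The two mechanisms could also offset each other, so the net effect is unknown. The figures show only that, at a correlation of 0.85, small systematic shifts matter. The plan should be amended, because the remedy is inexpensive and neither bias can be removed by analysis afterwards.

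**What to change.** Amend sections 4.d and 4.g of the Protocol.

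1. **Follow-up.** At 3 and 6 months, patients in all arms complete the questionnaires themselves in REDCap, unaided on a tablet if they attend in person, or by phone with the WCH research assistants, who are not told the arm. The specialist only schedules and reminds. Reword both sections so that they agree on who collects and who enters the data.
2. **Baseline.** Baseline questionnaires are submitted in REDCap after consent, before allocation is disclosed and before any kit introduction, including when the session is split.

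The cost is procedure wording and a few more phone surveys for assistants already in the plan; no staff, visits or patients are added. Patients will still know their own arm and may mention it on the phone, so some reporting bias remains and should be acknowledged when results are interpreted.
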